## Abstract

**Background and Objective:**

Our objective was to report on the design and essentials of the *Etoricoxib *protocol*- Preemptive and Postoperative Analgesia (EPPA) *Trial, investigating whether preemptive analgesia with cox-2 inhibitors is more efficacious than placebo in patients who receive either laparotomy or thoracotomy.

**Design and Methods:**

The study is a 2 × 2 factorial armed, double blinded, bicentric, randomised placebo-controlled trial comparing (a) etoricoxib and (b) placebo in a pre- and postoperative setting. The total observation period is 6 months. According to a power analysis, 120 patients scheduled for abdominal or thoracic surgery will randomly be allocated to either the preemptive or the postoperative treatment group. These two groups are each divided into two arms. Preemptive group patients receive etoricoxib prior to surgery and either etoricoxib again or placebo postoperatively. Postoperative group patients receive placebo prior to surgery and either placebo again or etoricoxib after surgery (2 × 2 factorial study design). The Main Outcome Measure is the cumulative use of morphine within the first 48 hours after surgery (measured by patient controlled analgesia PCA). Secondary outcome parameters include a broad range of tests including sensoric perception and genetic polymorphisms.

**Discussion:**

The results of this study will provide information on the analgesic effectiveness of etoricoxib in preemptive analgesia and will give hints on possible preventive effects of persistent pain.

**Trial registration:**

NCT00716833

## Background

To achieve an adequate postoperative pain therapy is a medical challenge. Acute postoperative pain is followed by persistent pain in 10-50% of individuals after common operations, such as groin hernia repair, breast and thoracic surgery, leg amputation, and coronary artery bypass surgery. Since chronic pain can be severe in about 2-10% of these patients, persistent postsurgical pain represents a major, largely unrecognised clinical problem [1]. There is a discrepancy between the results of many epidemiological surveys reporting persistent pain in a significant portion of postoperative patients despite the fact that very effective analgesic tools are available to treat postoperative pain [2,3]. Postoperative analgesia improves patients rehabilitation, shortens hospital stay, and potentially decreases postoperative complications [4]. In this context, the acute pain management team responsible for the patient's analgesic therapy can play an important role in improving the patient's surgical outcomes [5,6].

Preemptive analgesia has become one of the most promising strategies of pain management [7]. The precise definition of preemptive analgesia remains controversial. However, the explanatory concept behind it indicates that an analgesic intervention begins before the noxious stimulus arises which has beneficial effects reducing postoperative pain and the occurrence of postoperative pain [7]. From a physiological view of pain, physical injury generates a complex stress response that extends beyond the nervous system contributing to the experience of postoperative pain. This response comprises of neurotransmitters, peptides, endocannabinoids, cytokines, and hormones, all of which are operating in interdependent nervous, endocrine, and immune processes to cope with the injury [8]. The transition of acute postoperative pain into a chronic pain state is a complex process that not only involves the effects of one's physiological state but also involves psychological and social-environmental factors [6,9]. All these effects are supposed to induce plasticity in spinal and supraspinal structures contributed to the chronification of postoperative pain [10,11]. Therefore, in using preemptive analgesia there is a partial stopping to some of the influencing factors experienced; which in turn, may already prevent the sensitizing effects of the surgical procedure.

Systematic reviews suggest that current preemptive analgetic therapy, e.g. systemic non-steroidal anti-inflammatory drugs (NSAIDs), decreased analgesic consumption but not postoperative pain scores [12]. This effect is more pronounced when using invasive analgesia, e.g. epidural analgesia [12,13]. Nevertheless, NSAIDs failed to elicit significant effects in all of the outcome measured values in the reviews; affected selected variables were only mentioned. Although there is a widespread belief of the efficacy of preemptive analgesia among clinicians, large scale randomised controlled trials will be necessary to prove the current concepts.

A multimodal approach which combines several agents (non-opioid analgesics, opioids, local anaesthetics) and delivery techniques (intravenous anaesthesia, patient-controlled anaesthesia, epidural and regional blocks) is currently recognised as best practice in postoperative pain management [14]. Traditional, nonspecific NSAIDs are considered an important part of postoperative pain management, resulting in improved clinical outcomes. Otherwise their role is limited in the peri- and postoperative setting due to (a) platelet dysfunction, (b) renal impairment, (c) gastrointestinal disorders and (d) bleeding complications [15]. There are concerns especially with their effects on platelets which have limited their use in the immediate preoperative period [16]. The development of COX-2-selective agents has provided additional options for the management of acute pain. COX-2-inhibitors may offer benefits in the pre- and perioperative settings because of their selective inhibition of COX-2. Several studies report significantly lowered postoperative pain scores such as a significantly reduced dose of postoperative opioids [17-19]. In addition, their unique pharmacologic profile makes them a promising alternative to NSAIDs [20].

To our knowledge, there are only a limited number of publications examining the preemptive effect of COX-2-inhibitors on the intensity of postoperative pain. All these studies deal with orthopaedic surgery [21-23]. We therefore carried out a novel study design to examine these preemptive and postoperative analgetic effects of COX-2-inhibitors, in particular etoricoxib, in patients programmed for abdominal or thoracic surgery. In addition, we aimed to follow-up the occurrence of persistent pain.

## Patients and Methods

### Study Design

The study is a 2 × 2 factorial armed, double blinded, randomised placebo-controlled trial comparing (a) etoricoxib and (b) placebo in a pre- and postoperative setting. After randomisation, patients receive preemptive medication of either (a) or (b). Medication will be given postoperatively for additional three days. Additionally, all patients receive morphine administered through Patient Controlled Analgesia (PCA). Analysis of all records is performed by blinded evaluators. The total follow-up period per patient is 6 month. Trial registration is NCT00716833.

### Patients

For the included patients the following criteria must be met:

- Age ≥ 18 years

- Scheduled abdominal or thoracic surgery harming peritoneum or pleura

- ASA classification I or II according to the American Society of Anaesthesiologists

Main exclusion criteria are:

- Severe cardiac/pulmonary/renal or neurologic diseases

- ASA score > II

- Patients with insulin-dependent diabetes mellitus or other diseases influencing the peripheral sensibility (e.g. polyneuropathy, chronic pain syndromes)

- Regional blocks

- Continuous use of analgesics

- Pregnancy or lactation

- Uncontrolled hypertension

- Contraindications listed in the product information of etoricoxib, i.e. intolerance, ulcers or gastric bleeding, inflammatory bowel diseases, anaphylactic reactions

Information will be held on the vigil of surgery. If criteria are appropriate and patients want to participate, they give their written informed consent with sufficient time of consideration.

### Randomised treatment allocation, blinding and sample-size estimation

Patients are randomly allocated to either the preemptive or the postoperative treatment group. These two groups are each divided into two arms. Preemptive group patients receive etoricoxib prior to surgery and either etoricoxib again or placebo postoperatively. Postoperative group patients receive placebo prior to surgery and either placebo again or etoricoxib after surgery (2 × 2 factorial study design, Figure 1). The randomisation procedure into the two study arms was performed by the Institute of Medical Information Technology, Biometry and Epidemiology, University of Munich, Germany. The biometricians compiled an allocation list which was the basis for the pharmacists to prepare sequentially numbered envelopes containing two boxes of study medication for pre- and postoperative use. The boxes contained either a 120 mg dose of etoricoxibe or an equivalent placebo pill. After inclusion into the trial, the study physician assigned the content of the lowest numbered envelope to the patient. Neither the patient nor the study physician knew about the content of the boxes, the pills were not distinguishable. This procedure assured a complete blinding.

**Figure 1 F1:**
[figure not shown]
**Study Design**. Patients are randomly allocated to either the preemptive or the postoperative treatment group. Preemptive group patients get etoricoxib 120 mg p.o. prior to surgery (day 0, preoperative). After surgical intervention, depending on their respective allocation, patients receive either etoricoxib 120 mg p.o. or placebo for the next three postoperative days (day 1-2-3, postoperative). Postoperative group patients get placebo prior to surgery and continue afterwards with either placebo or etoricoxib 120 mg p.o. for three postoperative days (2 × 2 factorial study design). The listed outcome measures will be assessed at the marked time points respectively.

We conducted a 2 × 2 factorial-armed study which should prove the superiority of preemptive versus postoperative etoricoxib. The study was based on the moderate effective size of pre-emptive etoricoxib vs. post-operative etoricoxib in the reduction of the 48 hour cumulative morphine consumption. A sample size of approximately 60 patients in the two arms (i.e. 30 patients in each of the four arms) is anticipated taking a drop out rate of 10% into account (this is a conservative estimate based on the dropped out rate of 4% in the study by Sinatra et al. [19]). With this sample size we would permit a type I error of alpha = .05, and with the alternate hypothesis, the null hypothesis would be retained with a type II error of beta = .2 (i.e. power of 80%).

The calculation of the effective size is based on the data of Sinatra et al. [19]. The authors found a mean reduction of cumulative morphine consumption of 23 mg in the treatment group (total morphine dose 45 mg, SD 14) compared to the placebo group (total morphine dose 68 mg, SD 25).

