### Data Analysis

Descriptive analysis of the study population (including means, standard deviations, median and frequencies) will be made for all parameters.

Main outcome measures will be analysed with a 2 × 2 factorial ANOVA. Independent variables are time point of medication uptake and allocated study arm, dependent variable is the cumulative morphine consumption within 48 hours postoperatively.

Secondary outcome measures (QST, pain intensity) will be analysed equivalent, taking into account the test interval (repeated measurement ANOVA). ANOVA will be adjusted according to Bonferroni using t-test for post-hoc confirmation of significant alterations.

Ordinal scaled data will be analysed with Kruskal Wallis test confirming significance with chi2 test.

For analyses of associative coherence we will use Spearman's correlations coefficient, Wilcoxon-test or Kruskal Wallis test. All reports will be performed according intention-to treat analysis.

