## Study Design

We have chosen a 2 × 2 factorial design for the following reasons: the factorial design has several important features. Firstly, it has great flexibility for exploring the treatment effects in the trials. Whenever examining treatment variations, factorial designs are strong candidates as the design of choice. Secondly, factorial designs are efficient due to the ability to combine multiple studies into one rather than conducting a series of independent studies. Finally, factorial designs are the only effective way to examine interaction effects [53,54].

If the primary aim of a trial is to identify useful single treatments, then it could possibly be more cost effective to use a three-arm study than a 2 × 2 factorial design. In this trial, it is of interest to detect the treatment interaction, i.e. the opioid-sparing effect of a non-opioid treatment. The chosen study design has the power to identify such statistically significant differences between etoricoxibe and placebo treatments [55]. While the methods are developed for binary outcomes, they can be readily adapted to outcomes based on continuous, ordinal or time-to-event data using the methods for power calculation [55,56]. No attempt has been made to adjust for multiple comparisons. However, this can be achieved by simply changing the level of significance according to some recognised procedures such as the Bonferroni correction [55,57]. In our opinion, the study design allows to obtain specific results regarding the preemptive and postoperative analgesic effects of etoricoxib on (a) the cumulative morphine consumption and (b) other parameters as mentioned: predisposing characteristics influencing postoperative pain (inter alia by means of questionnaires), sensoric perception, genetic polymorphisms and others.

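### The superiority claim of preemptive over postoperative etoricoxib, and the 80% power attached to it, do not belong to the 60 vs 60 comparison or to any effect in the planned 2 × 2 ANOVA

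*Protocol article*

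**What the plan says.** All references are to the protocol article.

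- **Aim behind the sample size** (Randomised treatment allocation, blinding and sample-size estimation; text after Figure 1). The study is one "which should prove the superiority of preemptive versus postoperative etoricoxib". Its size rests on the "moderate effective size of pre-emptive etoricoxib vs. post-operative etoricoxib in the reduction of the 48 hour cumulative morphine consumption". The text gives about 60 patients per group (30 in each of four arms), 10% dropout, alpha 0.05 and 80% power.
- **Groups** (same section; repeated under Interventions). The preemptive group takes etoricoxib before surgery, then etoricoxib or placebo. For the other group: "Postoperative group patients receive placebo prior to surgery and either placebo again or etoricoxib after surgery".
- **Analysis** (Data Analysis). "Main outcome measures will be analysed with a 2 × 2 factorial ANOVA". The factors are the time of medication uptake and the allocated study arm. No contrast between individual arms is named for the main outcome.
- **Objective** (Abstract). The trial is described as "investigating whether preemptive analgesia with cox-2 inhibitors is more efficacious than placebo".

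**The concern.** The names of the two groups suggest a comparison of two timings of the same drug. Their composition does not give that comparison. Half of the postoperative group takes placebo throughout, and half of the preemptive group also takes etoricoxib after surgery. A difference between the groups shows what the preoperative tablet adds. By itself it does not show whether giving etoricoxib before surgery is better than giving it afterwards.

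Two things are at stake. A significant group effect could be taken as support for the timing claim when the timings do not differ. And the stated 80% power stands next to a claim that only two of the four arms address directly, with half the patients.

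**Working it through.** **Notation.** E = etoricoxib, P = placebo; preoperative treatment first. The arms are E/E, E/P, P/E and P/P.

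**Inputs from the article.** 30 per arm; 10% dropout, so 27 evaluable per arm and 54 per group; alpha 0.05; power 80%. The cited study gives 45 mg (SD 14) on drug and 68 mg (SD 25) on placebo.

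**Assumptions.** Two-sided testing (sidedness is not stated); d = 0.5 for the unquantified moderate effect; SD either pooled, √((14² + 25²)/2) = 20.26 mg, or 25 mg.

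**Step 1: the plan's own figure.** n per group = 2(1.960 + 0.842)²/d².
- d = 0.5: 62.8, so 63 evaluable, and 63/0.9 = 70 randomised (one-sided: 50 and 56).
- 23 mg with SD 20.26: 13 evaluable, 15 randomised. With SD 25: 19 and 22.

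None of these returns 60. Working backwards, 54 vs 54 has 80% power at d = 0.54, which is about 11 mg at SD 20.26. Also, the 23 mg is a difference between drug and placebo, not between timings.

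**Step 2: what the ANOVA can test.**
- Preoperative main effect: ½(E/E + E/P) − ½(P/E + P/P)
- Postoperative main effect: ½(E/E + P/E) − ½(E/P + P/P)
- Interaction: E/E − E/P − P/E + P/P
- Stated claim: E/P − P/E

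Subtracting the second line from the first gives E/P − P/E. So the claim is the difference between the two main effects, and none of the three ANOVA effects equals it. The loose factor labels do not alter this: four cells split into two pairs in only three ways, and each way is one of the three effects above.

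**Step 3: the group effect when the timings are equal.** Let each single course save 11 mg, so the true E/P − P/E is 0. Let the second course in E/E add all, half or none of a further 11 mg. The group effect is then ½[11 + (11 + extra)] − ½[11 + 0] = ½(11 + extra). Its standard error is SD × √(2/54), i.e. 3.90 mg at SD 20.26 and 4.81 mg at SD 25. Noncentral t with 104 df gives the chance of significance:

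| Extra saving in E/E | Group effect | SD 20.26 | SD 25 |
|---|---|---|---|
| 11 mg (additive) | 11 mg | 80% | 62% |
| 5.5 mg | 8.25 mg | 55% | 40% |
| 0 mg | 5.5 mg | 29% | 20.5% |

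The direct contrast E/P − P/E falsely favours preemptive dosing in about 2.5% of trials in every row.

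A check with the article's own means: set all three active arms to 45 mg and P/P to 68 mg. The group effect is 56.5 − 45 = 11.5 mg, significant in 83% of trials at SD 20.26 and 66% at SD 25.

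Under additivity the postoperative effect cancels from the group comparison. If preoperative dosing saved 11 mg and postoperative dosing 20 mg, the group effect would still be 11 mg and significant in 80% at SD 20.26.

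**Step 4: power for the stated claim.** With 27 vs 27 the standard error in SD units is √(2/27) = 0.272. At d = 0.5, power is 44% (43.8% with 52 df, 44.4% with the ANOVA's 104 df). Power reaches 80% near d = 0.77, about 15.6 mg at SD 20.26.

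**The case against.** **No decision rule is printed.** The article does not say that the preoperative main effect will be taken as proof of timing superiority. The planned model can estimate E/P − P/E, and a full protocol or analysis plan that is not shown may name that contrast. This stands. A reader might infer that the trial is committed to a false-claim procedure, and the article does not show that. It does print the aim and the power together and sizes them on the two groups, so the mismatch is in the text itself and is not an omission.

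**The wording may be shorthand.** The group labels follow the preoperative pill, so the aim could be loose language for preoperative drug vs preoperative placebo, which agrees with the Abstract. The design may then be intact. But the sentence refers to postoperative etoricoxib, which half of that group never receives, so it still needs correcting.

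**The group effect is not uninformative about timing.** A reader might infer that it is. It is one of the two components of the timing contrast, and with equal cells the two estimates correlate at 1/√2 = 0.71. What it cannot do alone is establish the contrast or its direction.

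**There are not three declared primary questions.** The Discussion's Study Design section says "In this trial, it is of interest to detect the treatment interaction", but this is a rationale for choosing a factorial design, and the article then glosses the interaction as an opioid-sparing drug effect. The clear conflict is between the Abstract and the sample-size text.

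**The size depends on chosen inputs.** This stands. The 11 mg is not in the article and is close to the value at which 54 vs 54 has 80% power, so the additive 80% largely follows from that choice. Only the range should be used. Likewise d = 0.5 is an assumption.

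**Conclusion.** The point holds as a mismatch between the stated claim and the planned test. The core is algebraic and needs no assumed effect: the claim is E/P − P/E, the 60 vs 60 comparison is preoperative etoricoxib vs preoperative placebo, and no effect in the ANOVA equals the claim.

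The consequence is conditional on the group effect being read as the test of the claim, which the 60 vs 60 sizing suggests. On that reading, with equal timings saving 11 mg each, it would be significant in about 29% to 80% of trials at SD 20.3 mg and about 21% to 62% at SD 25 mg, against about 2.5% for a false claim in favour of preemptive dosing with the direct contrast. The stated 80% power does not apply to the timing claim. With 27 per arm, power is about 44% if moderate means d = 0.5.

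**What to change.** In the sample-size text and in Data Analysis:

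1. State the primary hypothesis as preoperative etoricoxib vs preoperative placebo on 48-hour cumulative morphine, averaged over postoperative treatment. This agrees with the Abstract and uses 60 vs 60.
2. Attach the sample size and the power statement to that contrast, with the assumed effect size in figures.
3. Remove the claim of preemptive over postoperative superiority from the group comparison.
4. Report E/P vs P/E as a named secondary contrast with its 95% confidence interval. Give its power only together with the effect size assumed for it.

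The cost is that superiority of one timing over the other is no longer a confirmatory claim, and that a change to the hypothesis needs a protocol amendment. No further patients are needed. If the sponsor prefers to keep timing as the primary question, E/P vs P/E has to be named as primary and the trial re-sized. At an assumed d = 0.5 that means 70 randomised per arm, or 4 × 70 = 280 with four equal arms.

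### The sample-size justification conflicts with itself: a 'moderate' timing effect is attributed to data showing a large drug-versus-placebo effect, and the stated inputs do not yield 120 patients

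*Protocol article*

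**What the plan says.** All the relevant text is in the protocol article, under Randomised treatment allocation, blinding and sample-size estimation, in the two paragraphs after the Figure 1 legend.

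- **Effect and contrast:** the study was "based on the moderate effective size of pre-emptive etoricoxib vs. post-operative etoricoxib", on 48-hour cumulative morphine consumption. No number is attached to the effect.
- **Size:** about 60 patients in each of two main groups, 30 in each of four arms, with 10% dropout already allowed for. The Abstract gives the total as 120.
- **Error rates:** "With this sample size we would permit a type I error of alpha = .05". Power is put at 80%. Sidedness is not given.
- **Source:** one cited study supplies the effect size. It is reported as showing a "mean reduction of cumulative morphine consumption of 23 mg in the treatment group". The group figures behind that difference are 45 mg (SD 14) on active drug and 68 mg (SD 25) on placebo.

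The Data Analysis section plans a 2 × 2 factorial ANOVA for this outcome. The Interventions section says the postoperative group takes placebo before surgery and then either placebo or etoricoxib afterwards.

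**The concern.** A sample-size statement should lead from a named contrast and a numerical effect to N. Here the links do not join, in three ways.

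1. **Contrast.** The effect is said to be one of timing (the same drug before or after surgery). The data behind it compare drug with placebo, so they do not estimate a timing effect.
2. **Size.** The effect is called moderate, but the data cited for it give a large one.
3. **Groups.** Half of the 60 patients in the postoperative group receive placebo throughout. The comparison of 60 with 60 is therefore preoperative etoricoxib against preoperative placebo, averaged over the postoperative treatment. It is not preemptive against postoperative etoricoxib.

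At stake is what the 80% refers to. Depending on the reading, power runs from about 44% to above 99%, and no difference in mg is stated that corresponds to 120 patients.

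**Working it through.** **Inputs from the article:** means 45 and 68 mg; SDs 14 and 25 mg; alpha 0.05; power 80%; dropout 10%; 60 per main group and 30 per arm. Evaluable patients: 60 × 0.9 = 54 per margin and 30 × 0.9 = 27 per arm.

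**Assumptions not in the article:** d = 0.5 for 'moderate', and a two-sided test unless marked otherwise. Sample sizes and power use the noncentral t distribution. The factorial ANOVA main-effect F test agrees (73.0% with N = 108, 77.5% with N = 120).

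**Step 1. Can about 60 per group be reproduced from the cited data?**

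Pooled SD = √((14² + 25²)/2) = √410.5 = 20.26 mg. Then d = 23/20.26 = 1.14.

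Approximate n per group = 2(1.96 + 0.84)²/d² = 15.7/d². For d = 1.14 this rounds up to 13, or 14 by noncentral t.

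| SD used | d | Evaluable per group | With 10% dropout |
|---|---|---|---|
| 20.26 (pooled) | 1.14 | 14 | 14/0.9 → 16 |
| 25 (placebo) | 0.92 | 20 | 20/0.9 → 23 |
| 14 (treatment) | 1.64 | 7 | 7/0.9 → 8 |

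None is near 60. With 54 to 60 per group, power for 23 mg exceeds 99% at either the pooled SD or SD 25.

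**Step 2. Does a conventional moderate effect reproduce it?**

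With d = 0.5, two-sided, 80% power needs 64 evaluable per group, or 64/0.9 → 72 enrolled (144 in total). One-sided, it needs 51 evaluable, or 51/0.9 → 57 enrolled, which is close to the stated figure.

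| Analysed per margin | Two-sided power, d = 0.5 | One-sided power, d = 0.5 |
|---|---|---|
| 60 | 77.5% | 86% |
| 54 | 73% | 83% |

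**Step 3. What does the named timing contrast get?**

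Etoricoxib only before surgery against etoricoxib only after surgery is one arm against one arm. At d = 0.5, two-sided, power is about 48% with 30 per arm and 44% with 27.

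**Step 4. What can 120 patients detect with 80% power, two-sided 5%, after 10% dropout?**

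- Preoperative main effect, 54 against 54: d = 0.544. In mg this is 0.544 × 20.26 ≈ 11.0, with a range of 0.544 × 14 = 7.6 to 0.544 × 25 = 13.6.
- Single-arm timing contrast, 27 against 27: d = 0.777. In mg this is 0.777 × 20.26 ≈ 15.7, with a range of 0.777 × 14 = 10.9 to 0.777 × 25 = 19.4.

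**The case against.** The strongest reply is that the article never commits to d = 0.5 or to two-sided testing, so the 80% has not been shown to be false. That stands. With 54 per margin, d = 0.54 gives exactly 80% two-sided, and 0.54 could fairly be called moderate. A one-sided 5% test at d = 0.5 needs 57 enrolled per group, which fits a text that speaks of about 60 and of proving superiority. One could also suppose that the 23 mg was halved for a main effect: 11.5/20.26 = 0.57, with 83% power at 54 per margin. But the article states none of these routes, and the ANOVA F test it plans is non-directional.

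A reader might therefore infer that the trial has 73% power instead of 80%, or that it must enrol 144 patients. The document does not support either. The 73% needs d = 0.5, a two-sided test and 54 evaluable patients all at once. Nor does it follow that a null result could not be interpreted, since a confidence interval for the difference in mg would do that whatever the planning text says. It would also go too far to say that the cited study was used only for its SD, because the article says the effect size itself came from there.

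A second reply is that an article condenses a fuller protocol. That excuses the missing sidedness and formula taken alone. It does not excuse the conflict among the elements that are printed: no fuller text can make 23/20.26 moderate or turn a placebo comparison into a timing comparison.

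**Conclusion.** The point holds as an internal contradiction and a failure to reproduce N. The contradiction rests only on the article's own figures: the data are active versus placebo and give d = 1.14 (0.92 with SD 25), while the text claims a moderate effect of timing. The data would call for about 14 to 20 evaluable patients per group (16 to 23 enrolled), against about 60 stated.

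The loss of power is conditional. It is about 7 percentage points (80% to 73%) if 'moderate' is d = 0.5, the test is two-sided and dropout is 10%. It is 2.5 points if all 60 are analysed, and absent if the test is one-sided. If the named contrast is taken literally as single arms, power at d = 0.5 two-sided is about 44%. The choice of contrast therefore matters more than the dropout allowance.

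**What to change.** Rewrite the sample-size paragraphs, with N unchanged, so that they state the powered contrast, the sidedness, the SD and the detectable difference. Either of these would be consistent with 120 patients:

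- *Main effect:* with 54 evaluable patients per margin (60 less 10%), an SD of 20.3 mg and two-sided alpha 0.05, the trial has 80% power to detect 11.0 mg (d = 0.54) between preoperative etoricoxib and preoperative placebo. The detectable difference is 7.6 to 13.6 mg for SDs of 14 to 25 mg.
- *Timing contrast:* with 27 evaluable patients per arm and the same SD and alpha, the trial has 80% power to detect about 15.7 mg (d = 0.78) between etoricoxib only before and only after surgery.

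If the main effect is chosen, say openly that it replaces the preemptive-versus-postoperative contrast now named. Both differences are solved backwards from N, so the text should also say why the chosen one is worth detecting. State that the 23 mg is an active-versus-placebo difference and not an estimate of the timing effect. Remove the word moderate or give it a number.

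The cost is one paragraph, with no extra patients and no change to the planned ANOVA. The downside is that the stated power or detectable difference becomes less favourable, markedly so if the single-arm timing contrast is the one kept.
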